## Abstract

**Clinical trial registration:**

www.drks.de, number: DRKS00029937.

## Introduction

Transcutaneous auricular vagus nerve stimulation (taVNS) is a rapidly developing technique for non-invasive neuromodulation that was repeatedly used to both improve health and mitigate health burden (1). While the stimulators were initially implanted invasively, they are increasingly replaced by non-invasive stimulators which first studies used to treat neurological and psychiatric disorders with (2, 3). The non-invasive, transcutaneous stimulation of the auricular branch of the vagus nerve activates the nucleus tractus solitarii (4–6). This brainstem activation leads to a broad distribution of afferent information within several cortical and subcortical areas, including the serotonergic raphe nuclei, the cholinergic nucleus basalis Meynert the pedunculopontine nucleus, and the noradrenergic locus coeruleus (7–9). Accordingly, there is evidence that taVNS leads to modulation of the neurotransmitter system including the serotonergic, cholinergic and noradrenergic system, but also GABAergic systems (10–12). This widespread activation can be demonstrated with functional magnetic resonance imaging (fMRI) (10–13). After taVNS application not only subcortical areas such as the locus coeruleus and the nucleus tractus solitarii but also cortical areas like the postcentral gyrus, cerebellum, prefrontal cortex, insula, or anterior cingulate are activated (10, 13). This cortical modulation is considered a possible explanation of the reduction in seizure frequency in epilepsy patients treated with taVNS (14, 15). The beneficial effect of VNS on post-stroke recovery also suggests a modulation on the motor system, but very few studies have focused on this (16).

The cortical excitability of the primary motor system can be investigated non-invasively with transcranial magnetic stimulation (TMS). Several single and double-pulse protocols allow an assessment of the excitability as well as its inhibitory or faciliatory modulation (17–21).

To date, only a few studies have investigated the effect of taVNS on the motor system using TMS so far. Capone et al. (22) demonstrated an increase in inhibition, assessed with the short intracortical inhibition (SICI) in a small group of 10 participants. Additionally, a study by Mertens et al. (23) revealed an altered resting motor threshold (RMT) in a small group of 8 subjects. In a very recent study, the increasing SICI after taVNS could be confirmed in 30 healthy subjects using Bayesian statistics, but differences in taVNS intensity and data analysis hamper the generalizability of the results (24).

Hence, current evidence that taVNS might modulate the excitability of the motor cortex can be considered rather limited. Thus, the aim of this study is to provide an in-depth examination of the modulatory effect of taVNS on cerebral motor cortex excitability in healthy study subjects.

This protocol is intended to describe the appropriate background, methods, and procedures for the proposed study. A summary of study details as well as differences between this study protocol and prior studies can be seen in Table 1.

**Table 1 T1:** Study details and previous studies.

		**Planned study**
Capone et al. (22)	−10 healthy participants - Randomized placebo-controlled double-blind study - 60 min taVNS - Motor threshold, motor evoked potential amplitude, recruitment curve, SICI	−30 healthy participants - Randomized, sham-controlled, double blind study - 30 min taVNS - RMT, AMT, SICI, ICF - Tolerance and perception threshold verum and sham taVNS - TMS-EMG coupled
Mertens et al. (23)	−15 healthy male participants - TMS-EMG and TMS-EEG - Motor evoked potentals, TMS-evoked potentials, single and paired pulse TMS - 60 min taVNS - Maximun tolerated stimulation	
Van Midden et al. (24)	−30 healthy participants - Double-blind, sham controlled - taVNS at 100 Hz - SICI, SAI	

## Methods and analysis

### Study design

This is a single-center, prospective, double blind, sham-controlled trial evaluating the effect of taVNS on motor cortex excitability. To this end, this study uses four stimulation conditions: taVNS/sham stimulation at perception threshold and taVNS/sham stimulation at tolerance threshold applied in randomized order using a within subject design.

### Study population and recruitment

In total, 30 subjects will be included in the study. The subjects for the planned study are recruited around the University of Greifswald. The subjects will be recruited for the study by means of a verbal announcement. Due to the time required for the study, all participants will receive an expense allowance of 100 euros after completion of the study for their time.

### Inclusion/exclusion criteria

Participants will be eligible for the study according to the following criteria (see Table 2):

**Table 2 T2:** Inclusion and exclusion criteria.

**Inclusion criteria**	**Exclusion criteria**
Age > 18 years and < 60 years	History of neurodegenerative or other neurological disorders; epilepsy or history of seizures.
	Persistent cardiovascular diseases or skin diseases
	Intake of long-term medication of any kind (except for oral contraception)
	Implanted medical devices or metal
	Pregnancy

Eligible participants will provide written informed consent prior study inclusion and randomization.

### Interventions

The study consists of a structural magnetic resonance imaging (MRI) and of four experimental sessions in total, during which either verum or sham taVNS will be administered at different stimulation intensities. TMS motor physiological measurements will be conducted before and after each taVNS session.

TMS and taVNS will be performed by two administrators (TH or PK). The TMS administrator will be blinded to the taVNS intervention condition (verum or sham), and vice versa. Data collection will take place in the TMS lab. Each measurement (TMS/taVNS) will be performed by only one investigator (TH/PK), with the other investigator being in the room next to the lab to avoid unblinding. The participant will also be instructed to not tell anything about the taVNS to the investigator performing the TMS.

In sum, the administrator applying taVNS will have no knowledge about the TMS parameters. There will be a minimum interval of 1 week between each experimental visit to reduce potential carry-over effects of the previous taVNS.

#### Structural MRI

High-resolution structural MRI (3 Tesla Siemens Magnetom Verio, 32-channel head coil, T1-weighted sequence with 176 sagittal slices, voxel size 1 × 1 × 1 mm^3^) will be acquired and will be 3D-reconstructed to be used for neuronavigation during the TMS procedures. This allows for accurate replication of TMS stimulation target between experimental visits using MR-navigated TMS.

#### TMS administration

First, neuronavigation will be performed with a stereo-tactical infrared optical-tracking Polaris camera (Polaris System, Northern Digital, Waterloo, Ontario, Canada) and BrainSight (BrainSight TMS, Rogue Research Inc.). Neuronavigated TMS will be applied via two Magstim 200 stimulators connected to form a BiStim unit (Magstim Company, Dyfed, UK) before and after taVNS application. Here, a figure-of-eight coil (70 mm in wing diameter) will be held tangentially over the scalp with orientation of the handle angled 45 degrees in the sagittal plane. The coil will be positioned that a maximum-evoked motor evoked potential (MEP) can be derived (motor hotspot). The cortical area stimulated by the TMS coil will be digitally marked on the MRI and stored in the neuronavigation program to guarantee precise, navigation-based stimulation on all examination days. Baseline TMS will take place on each experimental visit day, followed by verum or sham taVNS and will be repeated immediately after taVNS administration.

Surface electromyography (EMG) will be derived over the right and left interosseus dorsalis I muscles using Ag/AgCl electrodes (Ambu, Ballerup, Denmark) measuring 10 mm in diameter. The EMG signal will be amplified (CED 1902; Cambridge Electronic Design, Cambridge, United Kingdom), band-pass filtered (20–1,000 Hz), recorded with a temporal resolution of 2 kHz (CED 1401), and stored for off-line analyses (Signal V4.09). During the TMS examination, the patient will sit relaxed in an examination chair while the hand will be positioned on a pillow for measuring. Measurements from the EMG will be used to assess motor physiology.

The following motor physiology outcome measures will be collected: resting motor threshold (RMT), active motor threshold (AMT), input-output curve [recruitment curve; (RC)], short intracortical inhibition (SICI), intracortical facilitation (ICF).

The RMT is the minimum applied stimulation intensity to derive MEPs with at least a 50 μV amplitude level in four out of eight trials in relaxation.

The AMT is the minimum-applied stimulation strength to derive visible MEPs in four out of eight trials with minimal tension on the target muscle (abduction of the index finger) with ~100 μV EMG.

For evaluation of the RC, 10 × stimulation each at an intensity of 90, 100, 110, 120, 130, 140, 150, and 160% RMT will be presented in an pseudorandomized order.

For the double pulse protocols, the intensity of the test stimulus is chosen to be at the maximum slope of the RC. The conditioning stimulus (CS) for SICI and ICF is set to 80% RMT. Here, the interstimulation interval (ISI) between the conditioning stimuli and the following test stimulus is 2 ms for inhibition, and, respectively, 10 ms for facilitation. In total, 15 single pulses and 30 paired pulses (15 each of SICI and ICF) will be administered in a pseudorandomized manner and amplitude magnitudes will be recorded and stored for off-line analysis after each trial.

The analysis will be conducted using Signal software Version 4.11 (Cambridge Electronic Design, Cambridge, UK). Fitting of RC will be based on the 10 trials per stimulus intensity using a sigmoid Boltzman function to each individual RC, thereby estimating MEPmax (plateau of RC), SLOPEmax (slope of RC, straight line fitted to RC at its inflection point) and stimulus intensity s50 to obtain a response of 50% of the maximum (25).

SICI is expressed as a percentage as % SICI = 100 – (C/NC × 100), where C and NC represent the corresponding mean of the conditioned (C) or non-conditioned (NC) test stimulus MEPs. ICF is expressed as % ICF = (C/NC × 100) – 100. Parameters for both hemispheres are determined.

#### taVNS administration

Verum or sham taVNS will be performed using a tVNS^®^L-device (tVNS Technologies GmbH, Erlangen, Germany). The stimulation stimulus will be applied via two round, iridium covered, 2 mm diameter titanium electrodes, which will be attached to the subject's left ear in different positions (taVNS: cymba conchae; sham: earlobe; before taVNS will be attached, the skin will be prepared using an alcohol wipe to clean the skin and remove skin particles). Left sided taVNS will be applied to avoid the theoretically possible effect on the heart rate by stimulating vagal parasympathetic fibers (25). During the study, each subject undergoes a total of four different taVNS examination modalities (verum or sham taVNS at varying intensities; each patient will be assessed the same time of day to prevent circadian bias). On the first day of the study, the individual perception threshold and tolerance threshold of taVNS will be determined for each subject after the first TMS. During this procedure, the subject will sit on a chair while the taVNS device is attached to the left ear (stimulation site: cymba conchae). Using the tVNS Research App (tVNS Technologies GmbH, Erlangen, Germany), an increasing current will be applied (100 μA steps each; minimum: 100 μA, maximum: 5,000 μA). The patient will indicate the point at which he or she feels stimulation for the first time. This corresponds to the perception threshold of the taVNS. The perception threshold will be noted and stored for further study sessions. After the determination of the perception threshold, the current will be increased by 100 μA steps until the subject perceives the stimulation as painful. The intensity will then be reduced again until the stimulation is well-tolerated by the subject (defined as a strong tingling sensation, without pain perception). This procedure will be repeated a second time. Subsequently, the main value of the four values (pain–strong tingling—pain—strong tingling) will be calculated. The result corresponds to the tolerance threshold. In a randomized sequence, one of the two stimulation intensities will be applied either to the cymba conchae (verum stimulation) or to the earlobe (sham stimulation). In total, this results in four different types of application: verum taVNS at the perception threshold, verum taVNS at the tolerance threshold, sham taVNS at the perception threshold, and sham taVNS at the tolerance threshold. In every session, one out of the four application types will be chosen in a randomized order.

Stimulation, regardless of intensity, will be delivered continuously for 30 min (pulse width: 250 μs, stimulation frequency: 25 Hz, 30 s on/30 s off) to the left ear of participants. Motion threshold: off, ramp-up: off, Buzzer: off.

The corresponding settings will be transferred to the device via the tVNS Research App (tVNS Technologies GmbH, Erlangen, Germany) and applied accordingly. For this purpose, a bluetooth connection with a mobile device will be established to the device. The data will be entered via the smartphone while the device will be stimulated via a type of headphones.

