**Determination of tVNS perception threshold and**	
**discomfort threshold**	
One of the interventions, randomized	One of the interventions, randomized
Verum taVNS (perception threshold)	Verum taVNS (perception threshold)
Verum taVNS (tolerance threshold)	Verum taVNS (tolerance threshold)
Sham taVNS (perception threshold)	Sham taVNS (perception threshold)
Sham taVNS (tolerance threshold)	Sham taVNS (tolerance threshold)
Navigated TMS	Navigated TMS
RMT/AMT	RMT/AMT
RC	RC
SICI/ICF	SICI/ICF

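### Day-1 threshold determination puts verum-site stimulation inside the pre-post window of the primary outcome, in sham sessions as well as verum

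*Protocol article*

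**What the plan says.** All places are in the protocol article.

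- **Timing.** Under taVNS administration, for day 1: "the individual perception threshold and tolerance threshold of taVNS will be determined for each subject after the first TMS". Table 3 lists the step ("Determination of tVNS perception threshold and" the discomfort threshold) under session 1 only, after the baseline measurements and before the randomized intervention. No TMS is listed between this step and the intervention.
- **Site.** During the step, "the taVNS device is attached to the left ear (stimulation site: cymba conchae"). The same section defines the two conditions by site: stimulation goes "either to the cymba conchae (verum stimulation) or to the earlobe (sham stimulation").
- **Intensity.** For the perception threshold, "an increasing current will be applied (100 μA steps each; minimum: 100 μA, maximum: 5,000 μA"). After that, "the current will be increased by 100 μA steps until the subject perceives the stimulation as painful". The current is then lowered to a strong tingling and the procedure is repeated, so pain is reached twice.
- **Carry-over.** Under Interventions: "There will be a minimum interval of 1 week between each experimental visit to reduce potential carry-over effects" of earlier taVNS.
- **Outcome and model.** The primary outcome is the post-pre change in SICI, sham against verum. Post TMS follows immediately after taVNS. The analysis is a repeated-measures ANOVA with factors time, stimulus and intensity.

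**The concern.** The primary outcome attributes the change between two TMS blocks to the condition delivered between them. On day 1 something else is also delivered between them: stimulation at the active site, up to pain, in everyone. A participant who draws sham on day 1 thus has a sham change measured across verum-site stimulation. The protocol asks for a week between visits to limit carry-over, yet on this day it describes no interval between verum-site current and a sham session.

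Two consequences are possible. If calibration has an effect of its own on SICI, whether from the site, the pain or arousal, session 1 has a different expected change from sessions 2 to 4, and the stated ANOVA does not separate it. If calibration produces part of the verum effect in sham sessions and adds little to a full verum session, the verum-sham contrast is pulled toward zero and a null result becomes hard to interpret.

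**Working it through.** **The plan's own figure.** Sample size section: N = 30, f = 0.18, power 0.80. Alpha, correlation and number of measurements are not stated; I assume 0.05, 0.5 and m = 8 (2 × 2 × 2 cells).

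- λ = f²·N·m/(1 − ρ) = 0.0324 × 30 × 8 / 0.5 = 15.55, on 7 and 203 df. Power is 0.821.
- The f that gives exactly 0.80 is 0.176, which rounds to the stated 0.18. At f = 0.18, 29 participants suffice.

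The figure is reproduced under these assumptions. It has no direct bearing on this point, because it does not describe the single verum-sham contrast of changes.

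**Exposure.** Inputs are 30 participants, four conditions each given once, two of them sham, and order drawn by lottery.

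- Sham sessions: 30 × 2 = 60.
- Probability that day 1 is sham: 2/4 = 0.5. Expected day-1 sham sessions: 30 × 0.5 = 15, and 15/60 = 25%.
- SD of that count, with independent draws: √(30 × 0.5 × 0.5) = 2.7.

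**Case A: calibration adds the same amount d to every day-1 change.** A participant's contrast is the mean of two verum changes minus the mean of two sham changes.

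- It moves by +d/2 if day 1 was verum and by −d/2 if day 1 was sham. The expected shift is 0.
- Added variance per participant: d²/4.
- Added SD of the mean contrast: d/(2√30) = 0.09d.

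There is no bias in expectation. Noise and a session-1 effect remain, and time, stimulus and intensity do not absorb them.

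**Case B: calibration gives day-1 sham a share k of the full verum effect and adds nothing to day-1 verum.** The expected contrast is multiplied by 1 − 0.25k. As an illustration, take a contrast with exactly 80% power in a two-sided paired test at N = 30 and alpha 0.05. This means a standardized difference of 0.529 and a noncentrality of 0.529 × √30 = 2.90 on 29 df.

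| k (assumed) | Factor 1 − 0.25k | Noncentrality | Power |
|---|---|---|---|
| 0 | 1.000 | 2.90 | 0.80 |
| 0.1 | 0.975 | 2.83 | 0.78 |
| 0.25 | 0.9375 | 2.72 | 0.75 |
| 0.5 | 0.875 | 2.54 | 0.69 |
| 1 | 0.750 | 2.17 | 0.56 |

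The value 0.529 is chosen to give 80% power; the protocol does not state it. The row k = 1 would mean that calibration alone equals a full 30-minute verum session.

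**The case against.** The strongest reply is that calibration is given to everyone on day 1 whatever is drawn, and that order is randomized, so its effect cancels. For an additive effect this stands, in expectation. It does not cover a saturating effect, and it leaves the added variance of Case A.

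A second reply is that calibration is probably short and is followed by 30 minutes of allocated stimulation before post TMS. In that TMS block SICI is listed after the thresholds and the recruitment curve, so any effect would have to last at least that long. This makes large values of k less plausible. It does not show that k is zero, because the protocol states neither the duration of calibration nor any effect of brief exposure.

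A third reply is that session terms and sensitivity analyses are commonly left to a statistical analysis plan, which is not shown. That is fair, and the absence of a session factor is not a finding by itself. The point rests on the schedule, which the article does fix.

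A reader might also infer that calibration unblinds day-1 sham participants, because they notice the electrode move from concha to earlobe. The documents do not support counting this here: every participant receives both sites over the four sessions, so the change of site is noticeable whenever calibration is done.

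**Conclusion.** The point holds as a design weakness. The schedule places verum-site stimulation, up to pain twice, inside the measurement window of the primary outcome on day 1, in an expected 25% of sham sessions. A reader might infer that the primary contrast is therefore biased toward zero. The documents do not support that as a fact: they establish exposure, not an effect on SICI. Bias requires a non-additive effect. Its size, 0 to 25% of the contrast for k from 0 to 1, depends on a quantity that cannot be derived from the documents. With an additive effect the cost is variance and a session-1 effect only. The power figures illustrate the saturating case and are not a loss from the planned f = 0.18.

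**What to change.** **Preferred.** Determine the thresholds outside the pre-post window, at a separate earlier appointment at least the protocol's own one-week interval before session 1. The MRI appointment would serve if it is held on another day. Table 3 lists MRI under session 1, so the cost is at most one short extra visit per participant. This is possible only for participants not yet tested.

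**If the schedule stays.** Analyse the primary outcome with a linear mixed model that includes session (first against later) and its interaction with time. This addresses the additive case. Also pre-specify a mixed-model sensitivity analysis of the verum-sham contrast without session 1, which addresses the non-additive case. The stated repeated-measures ANOVA cannot be used for the latter: without session 1 every participant lacks one of the four conditions, so nobody has complete data. The cost is a little analysis work and some precision, since the sensitivity analysis keeps 90 of 120 sessions (30 × 3 of 30 × 4).

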### Randomization

A lottery procedure will be used to randomize the order of the taVNS. The four possible intervention methods (verum/sham taVNS x perception and pain threshold) will be written down and placed in an envelope, so it is not visible from the outside what is written on each slip of paper. The examiner performing the taVNS will use the measure that is written on the paper. One measure per examination day will be administered, so each subject completes each of the four measures.

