### Statistical analysis

#### Sample size

Overall, only a few studies investigating cerebral motor excitability after taVNS stimulation exist (22–24). Therefore, the determination of the effect size regarding the effect of taVNS on cortical excitability can only be determined inadequately. The total sample size of 30 subjects was determined based on the sample sizes of the mentioned studies (Capone 10 participants, Mertens 15 participants, van Midden 30 participants) (22–24). According to our a priori power analysis using G-Power, this sample size is sufficient to detect small to medium effect sizes (*f* = 0.18) with a power of 0.80.

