#### Data analysis

According to our primary outcome measurement, a three-way repeated measure ANOVA with factors time (pre, post), stimulus (verum, sham) as well as stimulus intensity (tolerance, perception threshold) will be performed.

Additional ANOVAs for each exploratory outcome variable will be calculated using the same ANOVA model.

In case of violation of requirements for parametric methods, data will be transformed before analysis or appropriate non-parametric tests will be conducted. Data analysis will be conducted using IBM SPSS Statistics for Windows Version 25 (IBM), MATLAB (MathWorks, 2016) and R software (http://www.R-project.org).

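### Lottery order with no session term in the primary ANOVA lets session effects on the post-pre SICI change add avoidable noise to the verum-sham contrast

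*Protocol article*

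**What the plan says.** **Order.** Under Randomization: "A lottery procedure will be used to randomize the order of the taVNS". The four conditions are written on slips and placed in an envelope, and "One measure per examination day will be administered, so each subject completes each of the four measures". The taVNS administration section adds: "In every session, one out of the four application types will be chosen in a randomized order". Neither section describes balancing conditions over sessions, or over the condition that came before.

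**Model.** Under Data analysis, the primary outcome is analysed with "a three-way repeated measure ANOVA with factors time (pre, post), stimulus (verum, sham") and stimulus intensity. There is no session or period factor.

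**Outcome and timing.** The primary outcome is the post-pre change in SICI, verum against sham. Baseline TMS is repeated at every visit, and visits are at least 1 week apart. In session 1 only, after the first TMS and before the intervention, the perception and tolerance thresholds are determined at the cymba conchae by raising the current until it is painful, twice (taVNS administration; Table 3).

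**Size.** "In total, 30 subjects will be included in the study", and this number is said to be "sufficient to detect small to medium effect sizes (*f* = 0.18) with a power of 0.80".

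**The concern.** In a four-session crossover, whatever differs between sessions should be kept out of the treatment contrast, by balancing, by adjustment, or both. Here neither is described.

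The schedule gives a specific reason to expect such a difference. In session 1 every participant, including those who draw sham, receives current at the verum site inside the pre-post window. The session's own baseline is taken before that step, so subtracting it does not help. The 1-week interval between visits does not address it either.

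Two things follow if session 1 changes SICI differently from the other sessions. Each participant's verum-sham contrast moves up or down according to which condition fell in session 1, which enlarges the error term. In the one allocation that is realised, the estimate also shifts if verum and sham were drawn unequally often on day 1. The stated power is 0.80, so there is little margin for lost precision.

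**Working it through.** **1. The plan's own figure.** The article gives N = 30, f = 0.18 and power 0.80. It does not state alpha, the number of measurements or their correlation. Assume alpha 0.05, m = 8 measurements, correlation ρ = 0.5 and sphericity. With λ = f²·N·m/(1 − ρ) = 0.0324 × 30 × 8 / 0.5 = 15.55 on 7 and 203 df, power is 0.821. The f that gives power 0.80 at N = 30 is 0.176, which rounds to 0.18, so the figure is reproduced. With ρ = 0.5, m = 4 (0.619) and m = 2 (0.479) do not reproduce it.

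**2. Reference for the primary contrast.** For each participant let D = mean of the two verum changes minus mean of the two sham changes. If σ is the within-subject SD of a change, Var(D) = σ²/2 + σ²/2 = σ². On a paired t test (29 df, two-sided 0.05), 80% power needs a mean D of 0.529σ. All power figures below refer to that effect.

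**3. What reaches the contrast.** A session effect on SICI level is present in both the pre and post values of that session and cancels in the change. Only an effect on the change survives.

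**4. Variance added by a session-1 shift s (in units of σ).** D moves by +s/2 if verum is drawn in session 1 and by −s/2 if sham is. With random order this adds s²/4 to Var(D), so the SE is multiplied by √(1 + s²/4). Power is then taken from the noncentral t with effect 0.529/√(1 + s²/4).

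| Assumed s | 1 + s²/4 | SE | Power |
|---|---|---|---|
| 0.25 | 1.016 | +0.8% | 0.794 |
| 0.5 | 1.063 | +3.1% | 0.776 |
| 1.0 | 1.250 | +11.8% | 0.708 |
| 1.5 | 1.563 | +25.0% | 0.611 |

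A linear drift from first to last session of the same sizes costs less: 0.796 / 0.782 / 0.730 / 0.653.

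**5. Chance imbalance.** The number of participants with verum in session 1 is Binomial(30, 0.5), SD √7.5 = 2.7. A split of 18:12 or worse has probability 0.36, and 20:10 or worse 0.10. At 20:10 the estimate moves by (20 − 10)/30 × s/2 = s/6. For s = 1 that is 0.167σ, or 0.167/0.529 = 31% of the detectable effect; for s = 0.5 it is about 16%.

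**6. Which remedy does the work** (simulation, 4,000 runs per cell, session as a term in a change-score model):

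| Order | Session term | Power, s = 0.5 | Power, s = 1.0 |
|---|---|---|---|
| Lottery | no | 0.77 | 0.70 |
| Lottery | yes | 0.80 | 0.80 |
| Williams | no | 0.79 | 0.71 |
| Williams | yes | 0.82 | 0.81 |

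Under the lottery without a session term, type I error was 0.046 to 0.057 across the scenarios, and the mean estimate matched the true effect.

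Part of the recovery comes from the error df. The change-score model pools them: 120 changes − 30 participants − 3 for session − 3 for condition = 84, against 29. That alone moves the reference power from 0.800 to 0.817 with no session effect at all.

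**The case against.** The case against acting has several parts.

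- **Validity is intact.** Random order is a legitimate crossover method. A reader might infer that the lottery biases the verum-sham comparison or makes its test invalid. The documents do not support that: over repeated randomisations the estimate is unbiased and type I error is held. This stands.
- **The same-day baseline protects the outcome.** It does so for session effects on SICI level, such as familiarisation. A reader might infer that any visit-to-visit difference in SICI harms the contrast, and that would be wrong. The baseline does not protect against something that happens between it and the post measurement, which is where the session-1 titration lies.
- **The size is unknown.** The documents give no session effect. Up to 0.5 SD the loss is at most about 2.4 power points. This stands, and is why a range is shown.
- **The lottery is not the main cost.** At a 1 SD shift, Williams order without adjustment does no better than the lottery (about 0.71). This stands; the missing session adjustment is the larger part.
- **Carry-over.** Preceding conditions are left unbalanced, but the protocol sets at least 1 week between visits and takes a new baseline each time. Nothing in the documents shows that carry-over remains, so no loss is claimed for it.
- **A condensed article leaves detail elsewhere.** A fuller document may restrict the order or add covariates. But the article does name the factors of the primary model and describe the draw, and the point is made on those.

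**Conclusion.** The point holds as one about precision. The order is drawn without described balancing, the stated model has no session adjustment, and the schedule places a step specific to session 1 inside the window that defines the primary outcome. Any resulting session effect on the change inflates the error of the contrast and can displace the estimate in the realised allocation.

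The loss is negligible to small for a session-1 shift up to 0.5 SD (power 0.78 or more). It becomes material at 1 SD (0.71) and serious at 1.5 SD (0.61). These figures rest on the assumed shift, on a shift that is the same for verum and sham, and on a reference effect of 0.529 within-subject SDs. A session term would not remove an effect of titration that differs between verum and sham sessions; the documents give no basis for sizing one.

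This is a cheap improvement worth making, not a flaw that undermines the trial.

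**What to change.** 1. **Primary model.** Analyse the post-pre SICI change in a mixed model with a random participant effect and fixed effects for stimulus, intensity, their interaction, and session (1 to 4). Equivalently, add session × time to the pre/post model, with random terms for participant × time and for session within participant. A session main effect alone in the pre/post ANOVA does nothing: it takes the same value before and after, and leaves stimulus × time unchanged. The session adjustment can also be adopted for participants already randomised, and by itself brings power back to about 0.80.

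2. **Order, for participants not yet randomised.** Replace the lottery by a pre-generated list of the four sequences of a 4 × 4 Williams square, in randomised blocks of four, held in sealed envelopes for the taVNS operator. At N = 30 the sequences fall 8/8/7/7. That is near balance over sessions and preceding conditions; exact balance needs 28 or 32. This adds about 1 to 2 power points over step 1.

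**Cost.** 3 degrees of freedom for session, and preparation of the list. No extra participants, visits or measurements.
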